### Recruitment

We will recruit socially diverse practices to the trial using both the Scottish and English Primary Care and Diabetes Research Networks. We will make use of the network of practices in Lothian we have established during a previous blood pressure trial, who are familiar with the technology and have already expressed a willingness to take part. We will also use the networks and contacts provided by our grantholders to extend recruitment beyond Lothian to Kent and Borders. Training for the practices will be provided by the research team.

Diabetes registers in participating practices will be searched to identify potential participants with HbA1c>7.5% (58 mmol/mol). Potentially eligible patients will be sent the study materials by their general practice with a covering letter and asked to contact the researcher if they are interested in participating. Once a patient has indicated interest in participating they will be invited to a clinic in their general practitioner’s (GP’s) surgery run by a research nurse. At the initial appointment the nurse will go through the study information with the patient, take written informed consent (which will cover consent to have their eligibility checked as well as their consent to take part in the trial), check potential eligibility, ask the patient to complete a short questionnaire on their demographic characteristics, past and current self-monitoring of blood pressure and blood glucose, collect a blood sample for HbA1c and cholesterol measurement, a urine sample for sodium:creatinine ratio and initiate ambulatory blood pressure monitoring using the Spacelab Ambulatory Blood Pressure Monitor (ABPM) [28]. The nurse will also explain the process for recruitment and potential randomization if patients are eligible.

All patients will be loaned an ABPM with which they can monitor their blood pressure for 14 hours. However, if they wish they can delay collecting ABPM data until after the result of their HbA1C is available and their eligibility is confirmed. Once the HbA1c result is available, any ineligible patients will be telephoned to let them know that they do not need to return for a second appointment to gather baseline measurements. Patients’ ABPM results will be released to the practice.

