### Baseline measurements

At their second appointment, prior to randomization, participants will have the following baseline measurements taken: smoking history, height and weight, and exhaled carbon monoxide. In addition they will be asked to complete a range of questionnaires to collect information on anxiety/depression [29], quality of life [30], self-efficacy [31], medication adherence [32], physical activity [33], exercise tolerance [34], knowledge of managing diabetes [35] and ethnic group, based on categories included in the 2011 Census [36].

Randomization will be carried out remotely at the Edinburgh Clinical Trials Unit to ensure adequate concealment. We will use minimization with a random element based on age (<70 or ≥70 years of age), sex, location (that is, Lothian, Kent, Glasgow or Borders) use of two or more diabetes drugs, use of three or more hypertension drugs and glucose self-monitoring history in order to make sure that these factors are distributed equally between intervention and usual care groups. The allocated treatment code will be generated by the Edinburgh Clinical Trials Unit over the internet (with a telephone back-up option if required). The participant will then be informed about the arm of the trial to which they have been assigned and given appropriate information and demonstration of equipment if allocated to the intervention group. All randomized participants will be included in the intention-to-treat analysis. All participants, regardless of allocation group, will be seen by a healthcare professional from the practice trained in the management of type 2 diabetes who will assess current control, optimize management in line with Scottish Intercollegiate Guidelines Network and National Institute of Health and Clinical Excellence (NICE) guidelines and deliver a one-to-one standardized education session.

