### Intervention

Patients in the intervention group will be given blood pressure and blood glucose monitors and weighing scales which use Bluetooth to transmit readings via a (supplied) modem to a remote server. The user may securely access their record on the server at any time (either at home if they have internet access, or in a library or other public internet access point). Their GP and practice nurse will also be able to access this record via the Internet. Users will also receive regular (monthly) feedback based on their blood pressure and blood glucose over the past 10 readings which will be sent by post or email according to the patient’s wishes.

Participants will be trained in use of the equipment and the demonstration will be backed up by written information. The written information pack will also contain leaflets about initiating or maintaining lifestyle changes and how long it is likely to be before any lifestyle or medication change will have an impact on their rolling average blood pressure or blood glucose. The suggested lifestyle changes will include weight control, reducing salt in the diet and increasing physical activity.

The user will also be given contact details for the practice nurse and encouraged to make contact by email or by telephoning at specified times if their blood pressure or blood glucose remains high, to discuss their treatment. In the event of a very high blood pressure (>220 mmHg) or very high blood glucose levels (>15 mmol/l) patients will be asked to repeat the measurements and, if they remain high, to contact their practice urgently for advice. Patients recording very low blood glucose (<4 mmol/l) will be advised to eat or take a glucose drink and, if hypoglycemia persists, to contact the practice. Practice nurses will be encouraged to review the readings they are sent about patients whose blood pressure or blood glucose remains high or persistently low or who have not checked their blood pressure or blood glucose within the agreed timeframe on a weekly basis. Practice nurses may choose to contact the patient to offer further treatment or support and will be asked to record such contacts in the normal practice electronic record. The nurses will also be asked to transfer the current average blood pressure and blood glucose into the primary care record.

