Patients will be encouraged to check their blood pressure 10 to 20 times over the first seven days to establish a reliable average and then about 4 times a month if their average blood pressure is at or below the target of 130 mmHg. If blood pressure is above the target and any changes to lifestyle or medication are made, the users will be asked to undertake another more intensive period of monitoring (10 to 20 readings over seven days) after an appropriate time (usually 3 to 4 weeks depending on medication change) in order to establish the impact on the rolling average blood pressure. The guidance will not be restrictive as this tool is being provided for patients to use in order to understand their blood pressure better and to better manage their own health.

Patients in the intervention group will be asked to provide at least twice weekly measurements of morning and evening blood glucose and weekly measurements of morning weight. These measurements will be automatically forwarded to the study website and checked at least weekly by the practice nurse. Patients with high readings will be highlighted by the software for easy identification. The nurses will contact the patients by telephone, text or email to adjust therapy and reinforce lifestyle advice on the need for more or less intensive monitoring. Antihypertensive drug treatment may be altered every 4 to 6 weeks until mean blood pressure based on the last 10 readings is at or below the target of 130 mmHg. Treatment for diabetes will be altered according to the protocol based on guidelines every 4 weeks with the aim of maintaining consecutive fasting blood levels between 4 and 6 mmol/l. Patients who require the addition of insulin to their treatment during the course of the trial will be jointly managed by the practice nurse and GP along with specialist diabetes nurses at the local hospital (if appropriate) according to local practice, all of whom will have access to the telemetric data for patients in the intervention group. Algorithms for glucose and blood pressure management are given in the appendices.

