### Control group

Patients in the control group will receive leaflets with lifestyle advice and usual care, that is attending the practice nurse or GP for appointments as normal. They will be asked about their use of self-monitoring of blood pressure and blood glucose at baseline and follow-up. Patients with uncontrolled blood pressure in our recent audit saw the nurse or doctor three or four times on average in 6 months and we would anticipate a similar number of attendances for patients with both uncontrolled glycemia and blood pressure. Patients requiring insulin during the course of the trial will be managed jointly as above with specialist diabetes nurse support. Throughout the trial, patients will be reviewed according to clinical need by their normal clinical advisors. Clinical care in both groups for patients in Lothian will be in accordance with NHS Lothian protocols which are based on the recommendations of national and international guidelines, and in other areas according to NICE guidance. Therapeutic algorithms for both controls and intervention will follow guidelines, based upon the NICE guidelines [37] using a standard stepped treatment program for blood glucose.

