### Data collection and statistical analysis

Records will be kept of the numbers of practices and patients that were approached to participate in the study and the numbers and proportions of practices and patients that consented or declined to take part. Data from participating individuals will be entered from questionnaires and paper records by the researcher to a database. A random 10% sample will be checked for accuracy by independent trial staff. If we detect systematic errors we will re-enter all the data. Every attempt will be made to collect complete data on all of the participants.

Data analysis will be carried out by the Edinburgh Clinical Trials Unit. Data will be analyzed on an intention-to-treat basis, that is by allocation group regardless of compliance with the intervention. In the primary analysis we will remove patients with missing outcome data, but will perform sensitivity analyses to investigate the effect of this. Binary outcomes will be presented both as relative and absolute risk reductions. For HbA1c and blood pressure, and other normally distributed measurements that are taken at baseline and follow-up, adjustment for baseline measures will be performed using analysis of covariance. For the primary outcome, subgroup analyses will be performed based on sex, tertiles of age and socio-economic status (based on the Scottish Index of Multiple Deprivation derived from postcode) and tertiles of baseline HbA1c, home self-monitored systolic blood pressure and body mass index. These factors may all reasonably be hypothesized to influence the effect of the intervention. Subgroup analyses will be performed by adding any interaction between these factors and treatment into the analysis of covariance model and observing whether the fit of the model is statistically significantly improved. No interim analysis is planned.

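### The blood-pressure subgroup is defined by home self-monitored systolic pressure, which the protocol does not describe collecting in controls or before randomization

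*Protocol article*

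**What the plan says.** All references are to the protocol article.

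- **Data collection and statistical analysis.** Six factors are listed for subgroup analysis of the primary outcome: sex, age, socio-economic status and "tertiles of baseline HbA1c, home self-monitored systolic blood pressure and body mass index". The method is fixed too, with a gain in model fit as the criterion: "adding any interaction between these factors and treatment into the analysis of covariance model and observing whether the fit of the model is statistically significantly".
- **Intervention.** "Patients in the intervention group will be given blood pressure and blood glucose monitors and weighing scales". These patients are then asked to "check their blood pressure 10 to 20 times over the first seven days to establish a reliable average".
- **Baseline measurements.** After allocation, participants are "given appropriate information and demonstration of equipment if allocated to the intervention group". The measurements listed for the visit before randomization include no home blood pressure.
- **Control group.** On self-monitoring, the text for controls is: "They will be asked about their use of self-monitoring of blood pressure and blood glucose at baseline and follow-up".
- **Recruitment.** At the first appointment the nurse asks every patient about past and present self-monitoring, and will "initiate ambulatory blood pressure monitoring using the Spacelab Ambulatory Blood Pressure Monitor (ABPM"). The ambulatory monitor is lent to all patients for 14 hours.
- **Follow-up measurements.** Blood pressure at 9 months is again ambulatory, in both arms.

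**The concern.** A treatment-by-subgroup interaction compares the treatment effect across levels of a factor. The factor must therefore be known in both arms, and it should be fixed before allocation so that treatment cannot have changed it. As literally named, home self-monitored systolic pressure meets neither condition on the procedures described.

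An analyst following the text would have no control values to work with, and would have to drop the analysis or choose a substitute late, perhaps with the data in view. If instead the first week of intervention readings were used, patients would be grouped by a value that depends on how they took up the monitoring and on any early change in their care.

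This is not a complaint about detail left to an analysis plan. The article names a specific variable, and it does not match the article's own account of what is measured.

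**Working it through.** **1. Where each blood-pressure measure exists, by arm and time**

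| Measure | Intervention, before allocation | Control, before allocation | Intervention, after allocation | Control, after allocation |
|---|---|---|---|---|
| Home self-monitored readings | none described | none described | yes, from the first week of use | none described |
| Ambulatory (ABPM) | yes | yes | yes, at 9 months | yes, at 9 months |

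Questions about use of self-monitoring are put to all patients (Recruitment) and to controls (Control group). They are described as recording use, not blood-pressure values.

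**2. The plan's own sample size, for reference**

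Inputs from Sample size calculation: SD 1.4, difference 0.5, 5% significance (taken as two-sided), 80% power.

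- n per arm = 2 × (1.960 + 0.842)² × 1.4² / 0.5² = 2 × 7.85 × 1.96 / 0.25 ≈ 123.1, rounded up to 124. The t-test version gives 124.04, so 125.
- Power at 125 per arm is 80.6% (80.3% by t-test).
- Drop-out: 125 / 0.8 = 156.25, so 157 per arm and 314 in total, against about 320 planned.

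The stated figures reproduce, and none of them uses the subgroup variable.

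**3. Can the planned interaction be fitted?**

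The model has 7 columns: intercept, baseline HbA1c, treatment, two tertile indicators and two treatment-by-tertile products. Without the products it has 5.

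*Home readings in the intervention arm only.* Complete cases are 125 intervention patients and 0 controls. Treatment equals 1 in every row, so the treatment column duplicates the intercept and each product duplicates its tertile indicator. Four independent columns remain.

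- Rank with interaction: 4 of 7
- Rank without interaction: 4 of 5
- Degrees of freedom added by the interaction: 4 − 4 = 0

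*Baseline ambulatory pressure in both arms.* There are 250 rows.

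- Rank with interaction: 7 of 7
- Rank without interaction: 5 of 5
- Degrees of freedom added by the interaction: 7 − 5 = 2, so the test can be fitted

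**4. Would controls with their own devices rescue it?**

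The article gives no share, so I assume 10% to 30% of controls and, further, that their readings were obtained.

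- 125 × 0.10 = 12.5 and 125 × 0.30 = 37.5, so about 12 to 38 controls
- Divided by 3: about 4 to 13 per tertile

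The model could then be fitted, but on a small, self-selected set of controls.

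**5. What the repaired test could show**

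With 250 / 6 ≈ 41.7 patients per arm and tertile, and SD 1.4 without credit for baseline adjustment, the treatment effect within a tertile has variance 2 × 1.96 / 41.7 ≈ 0.094. The difference between the effects in the top and bottom tertiles has standard error √(2 × 0.094) ≈ 0.43. If the effect changes evenly across tertiles, the 2-df test has about 16% power for a top-to-bottom difference of 0.5 and about 52% for a difference of 1.0, in HbA1c percentage points. Even when correctly defined, this analysis is exploratory.

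**The case against.** The best defence is that this is only a mislabel. In the list, baseline most naturally governs all three items, since body mass index needs it as much as HbA1c does. The only blood-pressure measurement described before randomization is the ambulatory one, which patients take away and wear outside the clinic. On that reading the variable exists in both arms and the interaction can be fitted. This is plausible, and it rules out saying flatly that the analysis is impossible. It does not clear the text: the article elsewhere calls that measure ambulatory and describes self-monitoring as something separate.

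Three stronger readings are tempting, and the documents do not support them.

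- *Controls never have home readings, or all are documented as missing.* The article asks patients about self-monitoring of blood pressure, so it allows that some own a device. What can be said is that no collection of their readings is described. The figure of 0 out of 125 is an inference from that silence.
- *The factor is certainly post-randomization.* That holds only if baseline does not extend to this item. If it does extend, the text calls for a measurement that the baseline procedures do not provide.
- *The trial's main result is at risk.* It is not. The factor enters one of six subgroup analyses and no other part of the plan.

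The Discussion concedes that the trial cannot identify subgroups in which the intervention works better. Its examples are newly diagnosed diabetes and approaching insulin treatment, so it does not cover this point, though it fits the modest weight these analyses carry.

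**Conclusion.** The point holds for the variable as literally named. The article defines one of six subgroup analyses of HbA1c by a measurement that it does not describe collecting in controls or before allocation. On those terms the interaction contributes 0 estimable degrees of freedom, where 2 are intended. If the ambulatory measurement was meant, the test can be run and the fault is a wrong label. Either way the wording needs correcting.

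This rests on the data collection described in the article; a fuller protocol might add home readings for controls, but nothing shown suggests it. The rank results assume 125 completers per arm and no home readings from controls.

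The primary analysis, the secondary outcomes and the sample size are unaffected. Severity is moderate: should be fixed, not a bar to proceeding.

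**What to change.** In Data collection and statistical analysis, replace home self-monitored systolic blood pressure with **baseline daytime ambulatory systolic blood pressure (ABPM)**, and make clear that baseline applies to every measured factor in that list. Form the tertiles from both arms together.

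The measurement is already planned for all patients. Recruitment lets patients postpone it until their HbA1c result confirms eligibility, but Baseline measurements says that baseline data are collected before randomization, so it still qualifies. The analyst should confirm that each recording used predates allocation.

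The cost is one line of wording, with no new data and no change to trial conduct. It should be made, and dated, before outcome data are examined by arm, so that the choice of measure cannot be questioned later. If home readings in the intervention group are of interest, they can be described within that arm, not used as an effect modifier.

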### Sample size calculation

There were 4440 people with type 2 diabetes, an HbA1c of >7.5% and systolic blood pressure of ≥135 mmHg on the Lothian diabetes register in 2008. This group reflects approximately 16% of people on the register with type 2 diabetes. Their mean (standard deviation) HbA1c was 8.8% (1.4%) and their mean (standard deviation) systolic blood pressure was 149 mmHg (13 mmHg).

Using these values, we calculate that a randomized controlled trial with 125 people completing each arm with no change in values in the control group at the end of the trial would have 80% power at 5% significance to detect a 0.5% absolute fall in HbA1c and a 5 mmHg fall in systolic blood pressure in the intervention group. In an earlier trial of telemetric monitoring of blood pressure, 60% of patients on a practice hypertension register agreed to take part and 82% were retained within the trial [38]; we anticipate similar recruitment and retention rates in this study. We therefore plan to recruit a total of approximately 320 patients to ensure two final group sizes of 125 people which will provide sufficient power (assuming that up to 20% of people may drop out of the trial). We anticipate that this will involve recruiting 25 to 30 large general practices to participate in the study.

### Health economic analysis

The health economic analyses will assess the cost-effectiveness of the tele-supported self-monitoring compared to usual care. A cost-utility analysis (incremental cost per quality-adjusted life year) will be performed. The perspective will be the NHS. The benefits will include health outcomes measured in terms of quality-adjusted life years which will be derived from the responses to the EQ-5D [30]. Health service (GP/nurse consultations, telephone consultations, home visits, accident and emergency attendances, out-patient consultations, hospitalizations) and drug use over the trial period will be extracted from practice records to check the validity of self-reporting. Nurses will be asked how much time they use checking the website and on the telephone to patients. The costs of the tele-monitoring equipment and the set-up and support costs will be estimated using expert judgment. Resource use estimates will be combined with unit costs obtained from standard sources such as the Personal Social Services Research Unit. The results of the economic evaluation will be presented as an incremental cost-effectiveness ratio (cost-utility analysis). The evaluation will include both deterministic and probabilistic sensitivity analysis. Modeling of longer term costs and benefits will be explored using estimates from published studies including UKPDS [39]. Advice on the health economics analysis is being provided by [name] [name] from the Health Economics Research Unit at the University of Aberdeen and [name] from the Health Services Research Unit at the University of Edinburgh.

### Qualitative study

#### Participants

A sub-sample of participants in the randomized controlled trial will be recruited to the nested qualitative study. Up to 20 participants from the intervention group will be recruited for semi-structured interviews plus a further 10 to 12 for two focus groups. The purpose of the focus groups will be to allow the group to explore shared ideas and experiences relating to type 2 diabetes and hypertension and their experiences in managing it. The interviews with individuals will cover similar subjects but will allow private discussion of issues such as not using medication in the prescribed way (which people may not be willing to discuss in a public situation). A maximum variation sample in relation to age, social class, ethnicity (if ethnicity varies sufficiently between participants) and severity of type 2 diabetes and hypertension, plus level of use of the system will be sought.

